### Sample analysis

The principal investigator will process samples as follows. 4 ml of saliva will be obtained via passive drool into sterile CELLSTAR polypropylene test tubes (15 ml, catalogue number 188271; Greiner Bio-One, Frickenhausen, Germany), transported on ice and frozen and stored at −20 °C. Thawed samples will later be batch-processed and concentrated using equilibrated Sep-Pak C18 200-mg resin cartridges (catalogue number WAT 054945; Waters Corporation, Milford, MA, USA) before refreezing at −20 °C in 5-ml sterile Eppendorf tubes (catalogue number 0030119401, Eppendorf, Hauppauge, NY, USA). Triplicate OT concentrations will be batch-calculated using an OT enzyme-linked immunosorbent assay (ELISA) kit (catalogue number ADI-901-153A-0001; Enzo Life Sciences, Farmingdale, NY, USA) and an ELISA plate reader. Blood (2.5 ml) collected into PAXgene blood tubes (catalogue number 762165; BD Diagnostics, [name], USA) will be stored at −20 °C no sooner than 2 h after collection. Batch extraction of mRNA will later be performed using PAXgene blood RNA kits (catalogue number 762174; BD Diagnostics) and stored at −20 °C before cDNA libraries are made using iScript Advanced cDNA Synthesis kits (170-8843 Bio-Rad Laboratories, Hercules, CA, USA) and mRNA expression is determined by qRT-PCR using human OTR PCR primers (catalogue number VHPS-6555; Applied Biosystems, Foster City, CA, USA).

### Sample size

Mean antenatal EPDS scores extracted from a recent Australian study [111], as well as estimated post-intervention between-groups differences derived from a meta-analysis of two antenatal depression acupuncture studies [9], were used for a power calculation for this study. Using a power of 80 % and two-sided testing at a 5 % significance level, detecting a significant difference in end of intervention mean ± standard deviation (SD) EPDS scores of 8.9 ± 5 for the acupuncture group plus usual hospital care versus 13 ± 6.5 for usual hospital care will require a total recruitment goal of 75 participants. As high attrition rates have been reported for this population [144], an additional recruitment of 30 % has been added, resulting in a total goal of 96, or 32 participants per group.

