**Methods/design:**

In this pragmatic randomised controlled trial, we will compare individually tailored, flexible antenatal depression-oriented acupuncture with equivalent attention progressive muscle relaxation and routine antenatal depression hospital care. Eligible women at 24 weeks of gestation with Edinburgh Postnatal Depression Scale scores of 13 or more will be recruited from 2 antenatal clinics in South Western Sydney, Australia. The recruitment goal of 96 is powered to demonstrate a significant difference in Edinburgh Postnatal Depression Scale score severity between acupuncture and usual care, with intervention groups receiving weekly 1-h treatments for 8 weeks from 24 to 31 weeks of gestation. Mental health and quality-of-life assessments will occur at study commencement, intervention weeks 4 and 8 and 6 weeks post-natally via the collection of completed Edinburgh Postnatal Depression Scale scores, Depression, Stress and Anxiety Scale scores and World Health Organisation Quality of Life Scale scores. Adjustment to mothering will also be evaluated at 6 weeks post-natally using the Being a Mother Scale. A putative biomechanistic effect of acupuncture on the oxytocinergic system will additionally be examined by comparing baseline salivary hormone levels with those measured at intervention weeks 4 and 8, as well as leucocyte oxytocin receptor expression at baseline and intervention week 8.

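### The base of 75 participants does not follow from the stated two-sided inputs, which need 96 to 99, so the goal of 96 has essentially no attrition margin

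*Protocol article*

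**What the plan says.** The Sample size section of the protocol article sets the error rates: "Using a power of 80 % and two-sided testing at a 5 % significance level". The assumed end-of-intervention results are "EPDS scores of 8.9 ± 5 for the acupuncture group plus usual hospital care" "versus 13 ± 6.5 for usual hospital care". From these it concludes that acupuncture versus "usual hospital care will require a total recruitment goal of 75 participants".

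It then adds 30 % because attrition is expected to be high, and arrives at 96, which it gives as 32 per arm. The Randomisation and blinding section allocates 1:1:1 to three arms. So 96 is a three-arm total, and 75 is too: 25 per arm before the allowance.

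The abstract names the powered contrast: "The recruitment goal of 96 is powered to demonstrate a significant difference in Edinburgh Postnatal Depression Scale score severity between acupuncture and usual care". The Statistical analysis section plans an intention-to-treat analysis of variance, and the Outcome measures section plans multiple imputation of the primary endpoint using the K6.

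**The concern.** The article prints every input to its calculation, so the result can be checked in one line, and 75 is too small for a two-sided test. The error carries forward. If the base is too low, a final goal that looks as if it contains a reserve for dropout may contain none.

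The planned power of the acupuncture versus usual care comparison is at stake. A reader of the Sample size section would believe that the trial keeps 80 % power after losing about a fifth of its participants. If it does not, the chance of missing the assumed 4.1-point effect is larger than the 20 % that the section implies, in a population where the article itself expects many women to be lost.

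**Working it through.** **Inputs**, all from the Sample size section: difference 13 − 8.9 = 4.1; SDs 5 and 6.5, so the variances sum to 25 + 42.25 = 67.25 (root-mean-square SD 5.80, standardised difference 0.707); two-sided 5 %; power 80 %. Allocation of 1:1:1 is from Randomisation and blinding.

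**1. Requirement under the stated inputs.** n per arm = (z for alpha + z for power)² × (SD₁² + SD₂²) / difference².

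- Normal approximation: (1.960 + 0.842)² × 67.25 / 16.81 = 7.849 × 4.0006 = 31.4, so 32 per arm and 3 × 32 = 96.
- Exact t-test: power is 79.5 % at 32 per arm and 80.8 % at 33, so 33 per arm and 3 × 33 = 99.

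The stated 75 is not reproduced. It is 22 % below 96 (75/96 = 0.78) and 24 % below 99 (75/99 = 0.76).

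**2. What does give 75?**

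- One-sided 5 %, normal approximation: (1.645 + 0.842)² × 67.25 / 16.81 = 24.7, so 25 per arm and 75.
- One-sided 5 %, exact t-test: 79.4 % at 25 per arm and 80.8 % at 26, so 26 per arm and 78. This does not match.
- Two-sided exact t-test with a common SD of 5: 79.4 % at 24 per arm and 81.1 % at 25, so 25 per arm and 75.
- Two-sided normal approximation with 70 % power: 25 per arm and 75.

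Three different departures from the stated inputs reach 75. The stated inputs do not.

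**3. Other readings of 75.**

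- As a two-arm total (37 and 38 women): power is 85.6 % by the t-test, not 80 %, and the reading conflicts with a final figure of 32 per arm.
- As a three-group analysis of variance F test with the root-mean-square SD: 90 to 120 in total, depending on the mean assumed for the relaxation arm, which the article does not give.
- As a baseline-adjusted comparison: going from 31.4 to 25 needs 1 − r² = 25/31.4 = 0.80, so a correlation r of about 0.45. The article states no such correlation and no covariate.

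**4. Two-sided power by number evaluable per arm.**

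| Evaluable per arm | Share of 32 retained | Normal | t-test |
|---|---|---|---|
| 32 | 100 % | 80.7 % | 79.5 % |
| 25 | 78 % | 70.5 % | 68.8 % |
| 22 | about 70 % (32 × 0.7 = 22.4) | 65.0 % | 63.0 % |

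The row for 25 is the article's own base. The row for 22 is what remains if the 30 % is read as the proportion lost. At 25 per arm the difference detectable with 80 % power is 2.802 × √(67.25/25) = 4.6 points rather than 4.1.

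**5. The inflation step.** 75 × 1.3 = 97.5, while 96/75 = 1.28, so the increase actually applied is 28 %. This is minor beside the error in the base.

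**The case against.** The strongest reply is that the trial recruits 96, not 75. With 32 per arm analysed, two-sided power is 80.7 % by the normal approximation, so the recruitment goal meets the stated power if everyone contributes. The abstract claims only that 96 is adequate for the comparison. It quotes no power figure and mentions no attrition. This stands: a reader might infer that the abstract is false or that the trial's power simply is 69-70 %, and neither follows. The 69-70 % belongs to one scenario, 25 evaluable per arm.

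The second reply is that women without an end-of-intervention EPDS are not simply dropped. The analysis is by intention to treat, and missing primary data are to be imputed using the K6, which the Safety monitoring section has collected weekly in all groups. This also stands in part. Imputation may recover information, so the complete-case figures may understate power. The article gives no K6-EPDS correlation, however, so the gain cannot be quantified, and nothing in the calculation relies on it. It does not make 75 correct.

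A third point concerns cause. Because a one-sided normal-approximation calculation lands on 75, a reader might infer that the authors ran a one-sided test. The article specifies "two-sided testing at a 5 % significance level" and mentions no one-sided test. The match also fails with a one-sided t-test, and a common SD of 5 does equally well. The match is worth noting, but it does not show how the figure arose.

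Finally, the planned reporting of effect sizes with 95 % confidence intervals would show the imprecision of a null result, so it should not be assumed that such a result would be misread.

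**Conclusion.** The point holds as an arithmetic inconsistency within the Sample size section. The stated means, SDs, power and two-sided 5 % level need 96-99 evaluable women over three equal arms, not 75. The goal of 96 is therefore the bare requirement, with essentially no margin for attrition.

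Power depends on retention: about 80 % with no loss, about 69-70 % with 25 per arm evaluable, and about 63-65 % with 30 % lost. At those two levels of loss the chance of missing a true 4.1-point difference is about 30 % to 37 % instead of 20 %.

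These figures assume a comparison of two means with the printed SDs, equal allocation, equal loss across arms, no baseline adjustment and no gain from imputation. The document does not support any statement about why 75 was obtained, or any single figure for the power that the trial will deliver. It also gives no ground for a correction to the registry entry, which is not shown.

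**What to change.** In the Sample size section:

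- Replace 75 with 96-99 evaluable women in total (32-33 per arm), and say whether the normal approximation or the t-test was used.
- Drop the statement that 96 includes a 30 % attrition allowance on top of a base with 80 % power.
- If recruitment stays at 96, state power by retention: about 80 % with no loss, 69-70 % with 25 per arm evaluable, 63-65 % with 30 % lost. Note that any gain from the K6-based imputation comes on top and is not quantified.

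The abstract's statement that the goal is "powered to demonstrate a significant difference in Edinburgh Postnatal Depression Scale score severity between acupuncture and usual care" can stay if it is qualified, or read, as holding only with near-complete retention.

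The cost is a few sentences and a less favourable statement of power. No extra participants, endpoint change or analysis change is needed. Keeping both 80 % power and cover for 30 % loss would be a different decision with a real cost: 32/0.7 = 45.7, so 46 per arm (138 in total), or 33/0.7 = 47.1, so 48 per arm (144 in total).

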### Randomisation and blinding

Participants and practitioners are not blinded to the study; however, data entry and analysis will be blinded. The randomisation schedule was computer-generated to contain three groups of random numbers, enabling stratification for the three different models of antenatal care (obstetrician, standard and caseload midwifery) as well as to randomly contain ‘blocks of three’ within each group, acupuncture, PMR or usual antenatal hospital care (1:1:1). The schedule was generated by the school statistician ([name]) and concealed in opaque envelopes by an independent researcher from the National Institute of Complementary Medicine (NICM) ([name]).

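### Adding 30 % to 75 does not cover a 30 % loss: 96 recruits keep 75 women only if attrition is at most about 22 %

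*Protocol article*

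**What the plan says.** All the figures are in the Sample size section of the protocol article.

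- Design values: "Using a power of 80" per cent and "two-sided testing at a 5 % significance level".
- Assumed end-of-intervention means and SDs: "EPDS scores of 8.9 ± 5 for the acupuncture group plus usual hospital care", "versus 13 ± 6.5 for usual hospital care".
- Result before the allowance: this "will require a total recruitment goal of 75 participants".
- Reason for the allowance: "As high attrition rates have been reported for this population". No rate is given for the loss itself.
- The allowance: 30 % more recruits "has been added, resulting in a total goal of 96, or 32 participants per group".

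Randomisation and blinding gives the allocation as "acupuncture, PMR or usual antenatal hospital care (1:1:1"), so 75 is 25 per arm and 96 is 32 per arm. Outcome measures plans multiple imputation of missing primary-endpoint data using the K6, and Statistical analysis specifies intention to treat.

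**The concern.** Attrition is the only reason given for the 30 %, so a reader will take 96 as enough to leave 75 women after a 30 % loss. It is not. Losses are taken from the number recruited, so the requirement has to be divided by the expected retention. Multiplying it by one plus the loss rate always gives too small a figure, and the shortfall grows with the rate.

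At stake is the statement, repeated in the Abstract, that 96 is powered for acupuncture against usual care. If losses reach 30 %, the comparison rests on fewer women than the protocol itself says it needs, and a null result could be read as stronger evidence than it is. As the paragraph stands, nobody can tell from it how much loss the trial can absorb.

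**Working it through.** **Inputs** (Sample size; Randomisation and blinding): means 8.9 and 13, difference 4.1; SDs 5 and 6.5, sum of variances 25 + 42.25 = 67.25; two-sided 5 %; 80 % power; requirement 75; allowance 30 %; three equal arms.

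**1. Reproducing 96.**
- 75 × 1.30 = 97.5, or 25 × 1.30 = 32.5 per arm.
- Rounded down to 32 per arm, this is 32 × 3 = 96.
- The actual increase is 96/75 = 1.28, that is 28 %.

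So 96 comes from multiplying by 1.3 and rounding down.

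**2. What 96 protects against.**
- Largest loss that leaves 75: 1 − 75/96 = 21.9 %.
- Remaining after 30 % loss: 96 × 0.70 = 67.2, or 22.4 per arm.
- Recruits needed to keep 75 after 30 % loss: 75/0.70 = 107.1, rounded up to 108 (36 per arm).

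**3. Power for 4.1 points, two-sided 5 %, complete cases.** In the normal approximation, power = Φ(4.1/√(67.25/n) − 1.96). The t column uses the noncentral t distribution.

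| n per arm | Standard error | Power, normal | Power, t |
|---|---|---|---|
| 32 | 1.450 | 81 % | 80 % |
| 25 | 1.640 | 71 % | 69 % |
| 22 | 1.748 | 65 % | 63 % |

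At 22 per arm the difference detectable with 80 % power (normal) is (1.960 + 0.842) × 1.748 = 4.9 points, against the planned 4.1.

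**4. Dividing the shortfall between its two causes.**
- From 25 to 22 per arm, power falls from 70.5 % to 65.0 % (normal) or from 68.8 % to 63.0 % (t). This is about 6 points and belongs to the inflation step.
- From 80 % to 69-71 % belongs to the base figure. The stated inputs give n = (1.960 + 0.842)² × 67.25/4.1² = 31.4, so 32 per arm (33 with t), not 25. A one-sided test gives (1.645 + 0.842)² × 67.25/4.1² = 24.7, so 25.

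**5. What correcting the inflation alone would do.** 108 recruits with 30 % loss leave 108 × 0.70/3 = 25.2 per arm, so power would still be only about 70 %. Correcting both steps gives 32/0.70 = 45.7, so 46 per arm (138 in total), or 33/0.70 = 47.1, so 48 per arm (144 in total).

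**The case against.** The strongest reply is that the protocol never says it expects to lose 30 %. It gives 30 % as extra recruitment, and read literally the sum is nearly right. An intended loss of about 22 % fits the text equally well, since 75/96 is 78.1 % retained. The protocol also calls 75 a recruitment goal and not a number of completers. This stands as far as it goes. A reader might infer that the trial misses its own target at its own planned attrition rate, but the document sets no such rate, so the claim must stay conditional. The reply does not rescue the paragraph. On the literal reading the trial guards against only about 22 % loss, without saying so, in a population that it describes as having high attrition. Treating 75 as the number needed after losses is an interpretation, but the natural one, because the allowance is added on top of it.

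Second, one might call 96 a plain miscalculation because 30 % more than 75 is 97.5. The gap is half a woman per arm. Rounding up would be better practice, but this is only rounding.

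Third, a reader might blame the whole fall from 80 % to 63-65 % on the attrition allowance. The documents do not support that: 25 per arm, with no further loss, already gives only 69-71 %.

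Fourth, the analysis is not limited to completers. Under Safety monitoring the K6 is collected weekly in all groups, and imputation from it may recover some information under intention to treat. The complete-case figures are therefore somewhat pessimistic. How much is recovered cannot be judged from the document, and the sample size calculation takes no credit for it.

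**Conclusion.** The point holds in conditional form. Adding 30 % to 75 covers a loss of at most 21.9 %, not 30 %. If 30 % is the expected attrition, about 67 women remain (22 per arm), and 108 recruits would have been needed to keep 75. The inflation step costs about 6 points of power, from 69-71 % to 63-65 % for a 4.1-point difference. The rest of the shortfall from 80 % belongs to the base figure of 75 and should not be counted under this point.

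This rests on three assumptions: that 75 is the number needed after losses; that losses are equal across arms; and that power is computed on complete cases with the protocol's own means and SDs. The arithmetic is certain. That 30 % was meant as the expected loss is the natural reading, but not a stated one.

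**What to change.** In the Sample size section, state the assumed attrition rate as a number and replace the sentence on the allowance with wording such as:

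> The recruitment goal of 96 keeps 75 women if attrition is at most 22 %. At 30 % attrition about 67 remain (22 per arm), with about 63-65 % power for a 4.1-point difference in EPDS score, before any gain from imputation.

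Use n/(1 − attrition), rounded up to equal arms, for any future figure. Correct the base figure of 75 at the same time, because repairing the inflation alone would still leave about 70 % power. The power statement in the Abstract should be brought into line.

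The cost is one corrected paragraph with a less favourable stated power. Raising recruitment is a separate decision for the sponsor and does not follow automatically from the correction.

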### Statistical analysis

Descriptive statistics will be used to describe the characteristics of the study population. An intention-to-treat analysis will be undertaken [145], with between-groups differences explored using analysis of variance for the primary and secondary endpoints of depression, stress, anxiety, quality of life and OT/OTR. Effect sizes will be reported with 95 % confidence intervals, and results will be considered significant if *p* values are less than 0.05.

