### Outcome measures

Data and samples will be collected at various time points, including baseline, mid-intervention (week 4), end of intervention (week 8), birthing and hospital discharge (medical records) and 6 weeks post-natally. All questionnaires will be self-administered and collected by the principal investigator. The primary outcome endpoint, reduction in depression severity, will be assessed at baseline, at 4 and 8 weeks from trial entry and at 6 weeks post-natally via the EPDS, an extensively validated, clinically sensitive [138], 10-item self-report questionnaire. Additional secondary outcome endpoints will also be examined as follows :At the same time points as the EPDS, reduction in stress and anxiety will be monitored with the 21-item Depression Anxiety and Stress Scale (DASS-21) [139] and improvement to quality of life will be evaluated using the 26-item World Health Organisation Quality of Life Scale (WHO-QoL-26,) [140]. The DASS-21 is a short form of the clinically validated [141] and cross-culturally reliable [142] self-report measure of emotional states of stress and anxiety. The WHO-QoL-26 [140] is also an abbreviated form of this discriminant, content valid, internally consistent and reliable self-report measure for overall quality of life.Adjustment to parenting and maternal-infant bonding will be evaluated at 6 weeks post-natally via the 13-item Being a Mother Scale (BaM-13) [143]. The BaM-13 is a clinically discriminating, reliable and valid self-report tool specifically designed to enable early assessment of women’s experiences of motherhood.Maternal-infant outcomes such as gestational diabetes, mode of delivery, method of pain relief, labour augmentation, post-partum haemorrhage, breastfeeding level and duration, gestational age at delivery, birth weight, 1- and 5-minute Apgar scores, neonatal intensive care unit admission and need and reason for resuscitation and or intensive care will be assessed at delivery, discharge and 6 weeks post-natally.Salivary OT levels will be determined using saliva specimens collected by the principal investigator at baseline and at 4 and 8 weeks from trial entry. Leucocyte OTR messenger RNA (mRNA) expression will be assessed using blood collected by phlebotomists at local pathology centres at baseline and 8 weeks from trial entry.

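### Oxytocin and oxytocin-receptor endpoints are assigned analysis of variance with no stated scale and no baseline term, although baseline values are collected; a log-scale analysis of covariance would be a nearly free gain.

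*Protocol article*

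**What the plan says.** The protocol article's Statistical analysis section sets one method for the questionnaires and the laboratory measures together: "between-groups differences explored using analysis of variance for the primary and secondary endpoints of depression, stress, anxiety, quality of life and OT/OTR". It adds effect sizes with 95 % confidence intervals, and "results will be considered significant if *p* values are less than 0.05". It names no transformation and no covariate.

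Under Outcome measures, salivary OT comes from "saliva specimens collected by the principal investigator at baseline and at 4 and 8 weeks from trial entry", and leucocyte OTR expression from "blood collected by phlebotomists at local pathology centres at baseline and 8 weeks from trial entry". A baseline value is therefore planned for both.

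Under Sample analysis, two assays are named. For OT: "Triplicate OT concentrations will be batch-calculated using an OT enzyme-linked immunosorbent assay (ELISA) kit". For OTR: "mRNA expression is determined by qRT-PCR using human OTR PCR primers". The OTR primers are the only primer set listed, and no reference transcript or quantification method is given.

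The Sample size section concerns the Edinburgh Postnatal Depression Scale (EPDS) only. It arrives at 32 women per group after an allowance for attrition.

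**The concern.** An immunoassay concentration is positive and often right-skewed, with error that grows with its level. A qRT-PCR readout is a cycle number, which is already on a log2 scale. For both, an effect is most naturally a ratio. If raw concentrations or linear fold-values go into the analysis of variance, a few high values inflate the variance and the comparison loses power. If the analysis also uses the post-baseline value alone, it discards the part of the between-woman variation that the baseline sample could explain.

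Regulation of OT and OTR is one of the hypotheses at the end of the Background, yet the trial was not sized for it. Avoidable loss of precision makes an inconclusive result more likely, and such a result might be read as evidence against the mechanism. Leaving the scale open also allows a choice between raw and log results once the data are seen.

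**Working it through.** **Is there a figure to reproduce?** None for OT or OTR. The stated design values ("Using a power of 80 % and two-sided testing at a 5 % significance level"; EPDS "8.9 ± 5 for the acupuncture group plus usual hospital care versus 13 ± 6.5 for usual hospital care") belong to the primary outcome. What follows is a range under assumptions.

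**Inputs from the article.** Three arms, 1:1:1 (Randomisation and blinding); 32 per group (Sample size); significance at 0.05; OT at baseline, week 4 and week 8; OTR at baseline and week 8.

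**Assumed, because the article is silent.** Lognormal OT, equal CV in both arms, true between-arm ratio 1.5, CV 0.5 to 1.5, correlation r between log baseline and log outcome of 0.3 to 0.7.

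**Step 1. Log scale, no baseline, two arms.**
- Log-scale SD: σ = √ln(1 + CV²). CV 0.5 gives 0.472; CV 1.0 gives 0.833.
- Standardised effect: d = ln 1.5 / σ = 0.405/σ, so 0.858 and 0.487.
- Noncentrality: d·√(n/2) = 4d at n = 32, so 3.43 and 1.95.
- Two-sided 5 % t-test, 62 df: power 92 % and 48 % (simulation gives 49 % for the second).

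**Step 2. Raw against log.** The raw-scale figures need simulation (t-test on lognormal values, at least 20,000 runs per cell, good to about one percentage point):

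| CV | n per arm | Raw | Log |
|---|---|---|---|
| 0.5 | 32 | 89–90 % | 92 % |
| 0.8 | 32 | 53 % | 62 % |
| 1.0 | 32 | 38 % | 48–49 % |
| 1.5 | 32 | 20 % | 31 % |
| 1.0 | 22 | 27 % | 35–36 % |

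The last row takes 30 % loss from 32: 32 × 0.7 = 22.4.

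**Step 3. Add log baseline as covariate (CV 1.0, 32 per arm).**
- Residual SD = σ·√(1 − r²).
- r = 0.3: 0.833 × 0.954 = 0.794; d = 0.511; noncentrality 2.04; power about 52 %.
- r = 0.7: 0.833 × 0.714 = 0.595; d = 0.682; noncentrality 2.73; power about 76 %.

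At CV 1.0 the change of scale is worth about 10 points, and the covariate adds from about 3 points (r = 0.3) to about 27 (r = 0.7).

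**Step 4. Would a change-from-baseline analysis do as well?** Relative to σ², the variance is 2(1 − r) for change and 1 − r² for analysis of covariance. At r = 0.3: 1.40 against 0.91. At r = 0.5: 1.00 against 0.75. At r = 0.7: 0.60 against 0.51. The covariate has the smaller variance at each value, and change is worse than ignoring baseline when r is below 0.5.

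**Step 5. Does the pattern hold for a three-arm test?** A second simulation used the overall F test, with an effect in one arm of 0.71 log-SD. That value is borrowed from EPDS as an assumption: (13 − 8.9)/√((5² + 6.5²)/2) = 4.1/5.80 = 0.71. At 32 per arm, raw against log power was 84 % against 84 % (CV 0.2), 73 % against 83 % (CV 0.95) and 60 % against 83 % (CV 1.8). The direction is the same: no loss at low CV, a material loss near CV 1 and above.

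**Step 6. Validity.** Raw-scale type I error was about 4.0 % at CV 1.5 with 32 per arm in the two-arm simulation, and 3.4 % to 5.3 % across the three-arm settings. The raw test is slightly conservative under strong skew; it does not give excess false positives.

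**OTR.** No separate calculation is possible. If cycle-based values are analysed, the scale is already logarithmic and only the baseline argument applies. If linear fold-values are analysed, the scale argument applies as it does for OT.

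**The case against.** The strongest reply is that the article is silent on these details and does not state anything wrong. Analysis of variance is a family of models: run on log OT or on cycle-based values it is still analysis of variance, so the sentence does not compel a raw-scale analysis. Transformation of a secondary biomarker is commonly left to a statistical analysis plan. The Abstract also speaks of comparing baseline hormone levels with weeks 4 and 8, so baseline may be used in some way. All of this stands, and it is why the power loss is conditional.

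A reader might go further and infer that OTR will be left unnormalised, since only OTR primers are listed in a paragraph otherwise full of catalogue numbers. The article does not support that. It states neither that a reference transcript is omitted nor that RNA input is uncontrolled, and a laboratory procedure may cover both. Nor are the OTR primers the only assay named; an OT ELISA kit is named as well.

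A reader might also blame the choice of scale for any null oxytocin result. Even on the log scale, power at CV 1.0 is only about 48 to 49 % without a covariate. Most of that shortfall comes from a sample size set for EPDS.

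What survives is that the stated method, taken as given, includes no baseline term for endpoints measured at baseline and fixes no scale. A better specification is available at almost no cost.

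**Conclusion.** The point holds as a minor improvement to the analysis of secondary, mechanistic endpoints. Against raw post-baseline values, the log scale gains 2 to 3 points of power at CV 0.5 and about 10 at CV 1.0 (ratio 1.5, 32 per arm). Adding log baseline takes the CV 1.0 figure from 48–49 % to between 52 % and 76 % for correlations of 0.3 to 0.7. These sizes depend on lognormality, the assumed ratio, the CV and the correlation, none of which the documents give; at low CV the gain from the log scale vanishes. False-positive risk is not at issue. The documents do not show that a raw-scale analysis is intended, that baseline will be ignored, or that OTR goes unnormalised. The primary outcome is unaffected.

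**What to change.** In the Statistical analysis section, or in the analysis plan with a cross-reference:
- **OT:** take the mean of the triplicate, log-transform it, and compare arms by analysis of covariance with log baseline OT as covariate. Report ratios of geometric means with 95 % confidence intervals.
- **OTR:** analyse on the log2, cycle-based scale with the baseline value as covariate. Back-transform to a fold-difference with 95 % confidence interval.
- **Sample analysis:** confirm how OTR expression is normalised and, if a reference transcript is used, name it.

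The first two changes cost a few sentences and no extra data, since the baseline samples are already planned. The third is a cross-reference if a procedure exists; if a reference transcript is wanted and none is planned, it means one more primer pair on cDNA that is being made anyway. The article reports recruitment as ongoing and the assays as batch-run later, so the wording can be settled before results are seen. The one downside is that results are ratios of geometric means rather than differences in arithmetic means.
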